### Cost-effectiveness evaluation

Given the research design, we will seek to compare the cost of using ultrasound vs. battery of tests, although we assume that the use of battery of tests will be more economical.

A secondary analysis will be performed that will mainly include the following elements of analysis to complete an economic evaluation of both alternatives:

Resource consumption and costs involved in both alternatives.Using if possible, a social approach, differentiating it from the approach of the funder (Public Health Service).Include a sensitivity analysis of the most influential variables on the results.

### Sample characterization

Sociodemographic information (such as age, gender, level of education, perceived financial status, and frequency of social activity participation) is gathered using self-administered questionnaires as predictors of physical activity and fall history. These questionnaires are detailed in this paper.

### Data collection procedure

Recruitment will begin by contacting different centers participating in this study to ask geriatric physicians for potential candidates. In addition, center staff will also distribute flyers to increase the chances of reaching all potential candidates. Candidates who wish to participate voluntarily should express their interest by contacting the research team by phone or through the associate geriatricians at the different centers. After the first contact, the eligibility criteria for including potential participants in the study will be verified, additional information will be provided if needed, doubts will be resolved and, finally, the informed consent for participation will be signed before proceeding with data collection. Before starting the measurement, all investigators involved in the measurement evaluation performed the same protocol evaluation to ensure that all investigators performed the same procedures when evaluating different outcomes. All researchers who participated in the measurement evaluation had demonstrated experience in qualitative research and had five or more years of clinical practice experience.

After enrollment in the study, patients will undergo an extensive evaluation of previous described outcomes. Validated and translated questionnaires will be used, and ultrasound evaluation will be performed by an experienced evaluator with more than 10 years of experience. Expected and unexpected serious adverse events during outcome measurement will be collected and reported to the research team. The study design schedule is shown in Table 1.

**Table 1 t1:** Study design schedule.

**Timepoints**	**Enrollment**	**Assessments**
	**−1 week**	**0 week**
**Enrolment**		
Eligibility screen	X	X
Baseline	X	X
Informed consent	X	X
Medical history	X	X
Treatment history	X	X
Comorbidity	X	X
**Ultrasonography**	X	X
**Assessments**		
Manual grip strength	X	X
EQ-5D-5L	X	X
Barthel index	X	X
Trunk control test	X	X
BDI	X	X
VAS	X	X
GLIM	X	X
MRCSS	X	X
STAI	X	X
TSK	X	X
TUG	X	X
Adverse events		X

Timeline of procedures including enrollment, assessments, and ultrasound imaging. Abbreviations: EQ-5D-5L: EuroQol 5-dimensions 5-levels; BDI: Beck Depression Inventory; VAS: visual analogue scale; GLIM: Global Leadership Initiative on Malnutrition; MRCSS: Medical Research Council Sum Score; STAI: State-trait Anxiety Inventory; TSK: Tampa Scale of Kinesiophobia; TUG: Timed Up and Go test.

### Sample size calculation

The sample size was carried out based on the main objective and analysis of the study to evaluate which variables influence the level of dependence/independence through a multivariate logistic regression model, with Barthel index dichotomize as dependent variable, and manual grip strength, EuroQoL-5D, NPRS, cross sectional area and thickness of the rectus femoris, STAI, TSK and BDI as explanatory variable, for which a sample of 500 subjects was recommended according to Bujang et al. formula (100 + 50 × number of explanatory variables) and minimum sample size for logistic regression models [38–40].

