### Materials

Measurement variables evaluated in patients include:

Manual grip strength: The peak grip force was measured using a hydraulic hand dynamometer (JAMAR, Sammons Preston Rolyan, Sammons Court Bolingbrook, IL, USA) across a range of 0 to 90 kg. This device has been validated, shown to be reproducible, and deemed reliable for assessing grip strength in older individuals [22].Quality of life: measured with the EuroQol-5D, where mobility, personal care, daily activities, pain/discomfort, anxiety, or depression are assessed [23].Barthel Index: Assesses the level of independence of the subject with respect to the performance of activities of daily living [24].Trunk control test: Designed for the assessment of the patient's motor impairment [25].Intensity of Pain: Using the NPRS [26].Ultrasound image: The cross-sectional area and thickness of the rectus femoris muscle will be measured. In addition, contraction potential, contraction-relaxation velocity data will be taken by M-Mode ultrasound [27].The State-Trait Anxiety Inventory (STAI): Assessing state and trait anxiety [28].Kinesiophobia (TSK): Using the Tampa Kinesiophobia Scale, measuring fear of movement [29].Beck Depression Inventory (BDI): It measures depressive symptoms and the severity of depression [30].

Figure 1 illustrates the collection of variables in the older adult population of the study. Figure 2 summarizes the study workflow, from participant recruitment and assessments to the machine learning pipeline for prediction and analysis.

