### Statistical analysis

The R program version 4.3.1 will be used for statistical analysis. The level of significance will be set at *p* < 0.05. The distribution of quantitative variables, both baseline and outcome, will be tested with the Kolmogorov-Smirnov test with Lilliefors correction. Qualitative variables will be described in absolute values and frequencies and quantitative variables with mean and standard deviation.

Baseline and outcome variables differences using Barthel Index (BI) score dichotomized between dependent (BI < 60) and independent (BI > 60) patients [31] using *T*-test or U-Mann-Whitney for quantitative variables (depending on their distribution) and Fisher exact test for qualitative variables.

A multivariate analysis will be performed with a machine learning model through principal analysis using logistic regression, applying the model to 75% of the subjects and evaluating its accuracy in the remaining 25%, with the objective of creating a trained model that allows the development of therapeutic intervention plans that enable both the evaluation and treatment of patients. Model will be controlled by baseline variables with significant differences in univariate analysis.

Model will be constructed with dichotomized Barthel index as dependent variable and manual grip strength, EuroQoL-5D, NPRS, cross sectional area and thickness of the rectus femoris, STAI, TSK and BDI as explanatory variable. Logistic model will be selected instead of others used in machine learning (e.g. Random Forest, Support Vector Machines or Gradient Boosting) because it is computationally more efficient and faster and more easily interpretable.

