We will follow these steps to perform model: a) delete variables with high multicollinearity that is, presenting a Variance Inflation Factor (VIF) highest than 5, b) check model assumptions, if residuals are not normality distributed, they will be transformed with log or Box-Cox transformation, if they present heteroskedasticity or residuals remain not normally distributed, robust bootstrap model will be applied, c) random split of data set into training (75%) and test (25%), c) train the model with cross validation (5-folders will be applied) and elastic net features selection (it combines lasso and ridge features selection), e) model performance will be assessed with confusion matrix, Receiver Operating Characteristic (ROC) curve and calculation of Area Under a Curve (AUC), sensitivity/specificity and F1 score and f) evaluation of variable importance.

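### The sample size of 500 is justified for 8 variables fitted in all subjects, but the plan fits the model in 375 and leaves added covariates uncounted

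*Protocol article*

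**What the plan says.** All references are to the Protocol article.

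- **Sample size calculation.** The number is tied to the main objective, which is to "evaluate which variables influence the level of dependence/independence through a multivariate logistic regression model, with Barthel index dichotomize as dependent variable". The explanatory variables are listed as "manual grip strength, EuroQoL-5D, NPRS, cross sectional area and thickness of the rectus femoris, STAI, TSK and BDI as explanatory variable", which is eight if each enters as one term. The 500 comes from a "formula (100 + 50 × number of explanatory variables) and minimum sample size for logistic regression models". The value given by the second criterion, the minimum for logistic models, is not stated.
- **Statistical analysis.** The same outcome and the same eight variables define the model. It is to be built by "applying the model to 75% of the subjects and evaluating its accuracy in the remaining 25" per cent, and the numbered modelling steps repeat the 75/25 random split. The section adds: "Model will be controlled by baseline variables with significant differences in univariate analysis". The steps also include deletion of variables with a variance inflation factor (VIF) above 5, and elastic net selection with 5-fold cross-validation.
- **Implications and limitations.** Anthropometric indicators, with BMI as the example, are to be included in the analysis as an adjustment for confounding by subcutaneous fat.

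**The concern.** The formula gives a number of subjects for a number of explanatory variables. Its natural reading is that the subjects are those in whom the model is fitted. The sample-size paragraph uses all 500 for that purpose and all eight variables, so there is no slack. The analysis section then takes a quarter of the subjects out of the fit and allows further covariates in. Either change alone breaks the match between the justification and the analysis.

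At stake is whether the stated reason for 500 applies to the study's main analysis. The split also has a second cost. The confusion matrix, AUC, sensitivity, specificity and F1 score would rest on 125 subjects, while the Statistical analysis section wants a trained model that supports intervention plans.

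**Working it through.** **Inputs from the document**

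- Formula: n = 100 + 50k, where k is the number of explanatory variables (Sample size calculation).
- k = 8: grip strength, EuroQoL-5D, NPRS, cross-sectional area, thickness, STAI, TSK, BDI (same section).
- Total N = 500 (same section).
- Fitting fraction 0.75 (Statistical analysis).
- Additional covariates: an open number under the univariate rule (Statistical analysis), and BMI (Implications and limitations).

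**1. The plan's own figure.** 100 + 50 × 8 = 500. It reproduces exactly.

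**2. The fitting set.** 0.75 × 500 = 375 for training; 500 − 375 = 125 for testing.

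**3. What 375 supports.** (375 − 100)/50 = 5.5, so at most 5 variables. Check: 5 variables need 350, which fits; 6 need 400, which does not. For 8 variables the training set is 500 − 375 = 125 short.

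**4. Total needed if the split stays.** For 8 variables: 500/0.75 = 666.7, so 667.

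**5. Added covariates, with all subjects fitted.** (500 − 100)/50 = 8, so 500 covers at most 8 terms. One more gives 100 + 50 × 9 = 550, which is 50 more than planned. With the split as well: 550/0.75 = 733.3, so 734.

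**6. Precision of the AUC in the test set.** The document gives neither an expected AUC nor the share of dependent subjects. Both are assumptions here: a true AUC of A = 0.75, and 20%, 30% or 50% dependent. The Hanley-McNeil variance, with n₁ dependent and n₀ independent subjects, is

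Var = [A(1 − A) + (n₁ − 1)(Q₁ − A²) + (n₀ − 1)(Q₂ − A²)] / (n₁n₀),

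where Q₁ = A/(2 − A) = 0.6 and Q₂ = 2A²/(1 + A) = 0.6429. So A(1 − A) = 0.1875, Q₁ − A² = 0.0375 and Q₂ − A² = 0.0804.

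Example with 125 subjects and 20% dependent (n₁ = 25, n₀ = 100): Var = (0.1875 + 24 × 0.0375 + 99 × 0.0804)/2500 = 0.00362. The standard error is 0.060 and the 95% half-width is 1.96 × 0.060 = 0.118.

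| Dependent | Half-width, 125 subjects | Half-width, 500 subjects |
|---|---|---|
| 20% | ±0.118 | ±0.059 |
| 30% | ±0.100 | ±0.050 |
| 50% | ±0.086 | ±0.043 |

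The 500-subject column is a guide to what full use of the data could give. A resampling-based AUC does not have exactly this standard error.

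**The case against.** **Selection reduces the number of terms.** VIF deletion may remove variables, and cross-sectional area and thickness of the same muscle are plausible candidates. Elastic net shrinks or drops more, and a rule stated per variable does not map neatly onto a penalised fit. This stands in part: the shortfall is a mismatch with a rule of thumb, and it does not show that the model will fail. It does not remove the mismatch, because the sample-size paragraph counts all eight candidates before any selection. For 375 to suffice, VIF deletion would have to leave 5 or fewer terms, covariates included, and nothing in the document predicts that.

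**The formula is not the only criterion.** The paragraph also cites a minimum for logistic models. Its value is not given, so one cannot say that every criterion fails, only that the printed formula is not met in the training set. That the formula refers to the fitted sample is a reasonable reading which the document does not spell out.

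**The extra covariates are uncertain.** The univariate rule could add none. BMI appears only among the limitations, without naming this model. This stands as a caveat on the second part of the point; the first part, 375 against 500, does not depend on it.

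**Stronger readings that the document does not support.** A reader might infer that STAI must count twice, since Materials describes it as "Assessing state and trait anxiety". The model description does not say whether one or two scores enter, and such scoring detail may lie in the full protocol or analysis plan. A reader might also infer that 125 subjects are too few to measure accuracy. No precision target is stated, and a hold-out set combined with cross-validation is a recognised design, so the supportable word is imprecise.

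**Conclusion.** The point holds as an internal inconsistency. The calculation of 500 is correct, so it would be wrong to call it an arithmetic error; what differs is the analysis it is applied to. Under the printed formula, the 375 training subjects support at most 5 of the 8 named variables, a shortfall of 125 in the fitting set. Fitting all 500 would meet the formula for the eight variables, but any further covariate would exceed it.

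The first result needs only the reading that the formula refers to the fitted sample. The second needs at least one covariate to enter the model; the BMI adjustment, if it applies to this model, is enough. The precision figures rest on the assumed AUC and prevalences and show a halving of the half-width between 125 and 500 subjects, not a failure against a target. The plan should be corrected on this point, but nothing here shows that the study cannot proceed with 500.

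**What to change.** 1. Fit the model on all 500 and drop the single 75/25 split. Estimate AUC, sensitivity, specificity and F1 by bootstrap optimism correction or repeated cross-validation. Repeat every modelling step inside each resample: VIF deletion, any covariate selection that is kept, and elastic net.
2. Replace selection by univariate significance with a prespecified covariate list, and say whether BMI belongs to this model.
3. Restate the sample-size paragraph with the true number of candidate terms. Either keep the total at 8 or fewer, covariates included (so adding BMI means removing one of the eight), or state openly that 500 falls short of the cited formula, for example by 50 at 9 terms.

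If the split is kept instead, the formula asks for 667 subjects in total for 8 variables, or the paragraph should state the shortfall.

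The cost is revised wording, more computing, the loss of a separate hold-out set, and a somewhat less favourable stated justification. The Implications and limitations section, which describes internal validation by a separate test set, would need matching text. No extra patients are needed.

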### Data management

Every participant will receive an exclusive identification code, devoid of any personal details that could potentially reveal their identity. All data collected during the study will be securely stored in a locked cabinet at the local organizations, following a protocol aligned with the principles of Good Clinical Practice (GCP) guidelines. Upon completion of the study, the gathered data will be securely transferred to the research team's logistics department, where databases will be established. These databases will adhere to established protocols for archiving research materials, ensuring proper storage and accessibility.

### Dissemination policy

The study outcomes will be disseminated to the local organizations collaborating in the research, as well as to the professional sponsors focusing on promoting healthy aging. In addition, the findings will be made accessible to the general public through various platforms, such as official websites. The research team will also document the study results in numerous peer-reviewed publications for wider distribution and scrutiny.

### Data availability statement

Not applicable (this manuscript does not report data generation or analysis).

## DISCUSSION

The aim of this study is twofold: firstly, to investigate the correlation between muscle activation variables assessed via ultrasound and the comprehensive assessment of geriatric patients. This approach seeks to better understand how ultrasound findings may be related to the overall health and functional status of older patients. In addition, lastly published review found that ultrasound showed a low-to-moderate diagnostic test accuracy for sarcopenia, although included sample sizes was low (most studies less than 200 patients) and mostly only measured muscle thickness [41]. To counteract these limitations, this study has a large sample size with 500 patients and will measure muscle thickness but also cross-sectional area, as well as contraction potential and contraction-relaxation velocity with M-mode. Secondly, to analyze ultrasound images using histogram distribution to determine their correlation with mobi-mortality factors in frail patients. This approach will identify potential ultrasound markers that may be associated with a higher risk of complications in frail patients, as other studies found in the literature [42, 43].

To achieve these objectives, a study will be conducted on frail older adults, who will undergo a series of instrumental and functional tests designed to assess their functional capacity. Additionally, specific ultrasound images will be obtained to study sarcopenia and nutrition in this patient group. Subsequently, a comprehensive analysis of the correlation between all functional, ultrasound, and nutritional variables collected during the study will be conducted. This analysis will identify potential relationships between muscle activation, ultrasound image, and overall health and risk of complications in frail older patients.

### Implications and limitations

The potential implications of this study are substantial for both clinical practice and public health. The integration of ultrasound-derived muscle parameters with functional and psychological assessments, analyzed through machine learning, offers a scalable and cost-effective approach for the early detection of frailty. This may enable clinicians to stratify risk and tailor interventions in community-dwelling and institutionalized older adults, enhancing preventive care and reducing adverse outcomes associated with frailty.

Nonetheless, the study presents several limitations. First, the ultrasound measurements are operator-dependent, which introduces a risk of inter-rater variability. To mitigate this, we ensured strict standardization of procedures and training across all sites, along with reliability testing. Second, although the machine learning model will be internally validated using cross-validation and a separate test set, no external validation in a different population is planned in this protocol. Third, as participants are recruited by convenience sampling from institutional settings, there is a potential for selection bias and limited generalizability to broader older adult populations. Fourth, the accuracy of ultrasound imaging can be affected by the presence of subcutaneous fat, particularly in individuals with overweight or obesity. Excess adipose tissue may reduce image clarity, impairing precise delineation of muscle boundaries and affecting measurements of thickness and cross-sectional area. To address this limitation, we use a standardized acquisition protocol with high-frequency probes and minimal compression, and we plan to include anthropometric indicators such as body mass index (BMI) in the analysis to statistically adjust for this potential confounder. Lastly, while the current model focuses on predicting dependence based on the Barthel Index, other frailty dimensions (e.g., cognitive, social) may not be fully captured. These limitations will be addressed in future longitudinal studies with broader inclusion criteria and external validation.
